## Oversight and monitoring

### Composition of the coordinating centre and trial steering committee {5d}

The CI will assume responsibility for the overall management of the trial and delivery of the work. The CI will lead the core research team (including contact with the ethical committee, the trial manager, and research assistants), which will meet monthly via videoconference and presential meetings and receive input from the broader research group. The Clinical Studies Center of Medicine Faculty at Universidad del Desarrollo (Chile) will monitor all aspects of the conduct and progress of the trial, ensure that the protocol is adhered to, and take appropriate action to safeguard participants and the quality of the trial.

### Composition of the data monitoring committee, its role, and reporting structure {21a}

A Data Monitoring Committee (DMC) was deemed unnecessary due to the minimal risk posed to participants and the trial’s small scale.

### Adverse event reporting and harms {22}

#### Risk monitoring

To identify potential risk issues, our research assistants will conduct a screening every 48 h after the completion of the intervention sessions. This screening will involve checking the skin condition on the skull where the electrodes were placed and mild headache. These cautions are important to ensure no adverse effects or complications from the intervention and mitigate potential risks to the participants.

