**Methods:**

This study is a phase IIb randomised, double-blind clinical trial with a 3-month follow-up period. The study participants will be 62 participants diagnosed with MCI, aged over 60, from Valparaíso, Chile. Participants will receive an intervention combining twelve cognitive training sessions with tACS. Participants will receive either tACS or placebo stimulation in eight out of twelve training sessions. Sessions will occur twice weekly over 6 weeks. The primary outcomes will be electroencephalographic measurements through the prefrontal theta oscillatory activity, while the secondary effects will be cognitive assessments of WM. The participants will be evaluated before, immediately after, and 3 months after the end of the intervention.

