### Intervention description {11a}

In the CCTP, the patients will be organised into groups composed of three participants. The patients will realise a combined electrical stimulation and cognitive training programme. That contemplates 12 WM training sessions based on tasks of storage and manipulation of verbal and visuospatial information, with a frequency of twice a week for 6 weeks, completing a total of 12 sessions in presential format. Concomitantly, the participants will receive real electrical stimulation for 10 min during a verbal working memory task. The intervention will be delivered by trained personnel in this technique and an assistant to groups. This electrical stimulation protocol includes 10-s periods of phase-in and 10 s of phase-out and will be done in parallel with the cognitive intervention programme in sessions 3, 4, 5, 6, 7, 8, 9, and 11. The electrical stimulation will be applied with two 3 × 1 arrays of electrodes. The central stimulation electrodes will be positioned in F3 and CP3 (according to the international 10–20 system). The AC stimulation will be one mA from the baseline to the stimulation peak. The stimulation will have a gamma sine waveform (80 Hz) over the positive phase of the theta oscillation[33] individualised for each patient ranging from 4 to 8 Hz and the phase-locked between arrays [36, 37]. The electrode impedances will always be maintained under 10 kOhms.

Participants in the control group (TCTP) will start a cognitive intervention programme identical to the treatment group and will be organised into groups of three participants. Still, unlike the treatment group, they will receive placebo electrical stimulation, i.e. an electrical current will be applied for a short period at the beginning of the session (30 s). Then, the electric stimulation will be stopped. This procedure induces a sensation in the skin similar to real electric stimulation without generating a detectable impact on the brain state. They will be performed parallel to the cognitive intervention programme in sessions 3, 4, 5, 6, 7, 8, 9, and 11.

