## Assignment of interventions: blinding

### Who will be blinded {17a}

The person responsible for generating the random assignment sequence list must be made aware of the people who recruit and evaluate the participants. This generated sequence will be blind until the interventions are assigned. The type of masking will be double-blind since both the participants and the professionals who perform the pre-post evaluation will. For technical reasons, professionals administering electric interventions are not blinded to the type of electrical stimulation (i.e. real or placebo) being applied. The statistician analysing outcome data will remain blind to treatment allocation throughout the analysis, which will be conducted with groups indicated by an anonymised code.

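### The only active harm check described sits at 48 h, is ambiguously worded and is not tied to any existing visit, so short-lived effects may be under-counted

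*Protocol article*

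**What the plan says.** The Risk monitoring part of the protocol article (Adverse event reporting and harms {22}) sets one active check: "our research assistants will conduct a screening every 48 h after the completion of the intervention sessions". Its content is "checking the skin condition on the skull where the electrodes were placed and mild headache". The next part of the same section names the same two items as the expected hazards. It adds, without a time point or an active question, that possible adverse events and unintended effects will be documented and reported to the ethics committee.

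Intervention description {11a} sets the timetable: training runs "with a frequency of twice a week for 6 weeks, completing a total of 12 sessions in presential format". Real stimulation "will be done in parallel with the cognitive intervention programme in sessions 3, 4, 5, 6, 7, 8, 9, and 11", and the placebo arm has the same list: "They will be performed parallel to the cognitive intervention programme in sessions 3, 4, 5, 6, 7, 8, 9, and 11". Real current lasts 10 min per session and placebo current 30 s. Trained personnel and a group assistant deliver the sessions. Weekdays are not given.

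Who will be blinded {17a} says that "professionals administering electric interventions are not blinded to the type of electrical stimulation". It does not say whether the research assistants who do the screening know the arm.

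**The concern.** A harm check should be placed where it can be carried out as written and where it can see the effects it is meant to detect. This rule is weak on both counts.

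- **Wording.** The phrase about every 48 h can mean one check, 48 h after each session, or a check repeated every 48 h with no stated end. Two assistants could follow it differently and produce counts that cannot be pooled.
- **Placement.** With sessions twice a week, a 48 h point often falls on a day with no visit. The scalp item suggests an inspection in person, yet the article mentions no visit for it. Participant timeline {13} describes none. The retention plan {18b} lists evaluations, intervention and follow-up as the on-site sessions with reminders and transport.
- **Timing.** Effects felt during or just after the current may have passed by 48 h. The headache item then depends on recall over two days, in people enrolled for cognitive impairment.

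At stake is the completeness of the harm counts for the two hazards that the protocol itself expects.

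**Working it through.** **Inputs.** Two sessions a week for 6 weeks; stimulation in sessions 3 to 9 and 11 (Intervention description {11a}); 62 participants (Sample size {14}); check at 48 h (Risk monitoring).

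**The plan's own count.** 2 × 6 = 12 sessions. The list 3, 4, 5, 6, 7, 8, 9, 11 has 8 entries. This agrees with the abstract: "Participants will receive either tACS or placebo stimulation in eight out of twelve training sessions".

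**Can the 48 h point meet a training visit?** This part assumes, as the documents do not, that the check is done only at training visits and that the two weekdays are fixed.

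- Odd-numbered sessions open a week and even-numbered sessions close it. If the gap within the week is g hours, an odd session is followed after g hours and an even session after 168 − g hours.
- Odd stimulation sessions: 3, 5, 7, 9, 11 (five). Even stimulation sessions: 4, 6, 8 (three).
- The 48 h point meets a visit for the five odd sessions only if g = 48. It meets one for the three even sessions only if 168 − g = 48, that is g = 120.

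| Gap within week | Gap to next week | Met, of 8 | Not met | Not met × 62 |
|---|---|---|---|---|
| 24 h | 144 h | 0 | 8 | 496 |
| 48 h | 120 h | 5 | 3 | 186 |
| 72 h | 96 h | 0 | 8 | 496 |
| 96 h | 72 h | 0 | 8 | 496 |
| 120 h | 48 h | 3 | 5 | 310 |

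**Relaxing the fixed weekdays.** On Monday to Friday the gap across a weekend is at least 72 h, so the even sessions never qualify and the maximum stays at 5. If Saturday is used and weekdays vary, the maximum is 7. One example is Thursday/Saturday in weeks 2 and 4, Monday/Wednesday in weeks 3 and 5, and any 48 h pair in week 6. All five odd sessions qualify, and so do sessions 4 and 8 (Saturday to Monday). Only session 6 does not.

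**Relaxing the visit assumption.** If each check is a separate contact, coverage is 8 of 8. The number of such contacts is at most 8 × 62 = 496, counting only stimulation sessions, one check per session and full attendance.

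So the documents allow anything from 0 to 8 of 8. The last column of the table counts checks that fall outside a training visit, not checks that are lost.

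**Effect on the harm comparison.** Let p₁ and p₀ be the true proportions with an event in the real and placebo arms, and r the share of events that reaches the record, equal in both arms. The recorded difference is r·p₁ − r·p₀ = r(p₁ − p₀). If r is below 1, both counts and their absolute difference shrink, even though harms are sought in the same way in both arms. The documents give no per-session headache risk and no recall rate, so no value of r can be derived from them and I give no headache count.

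**The case against.** The best defence is that the article does not tie the check to the next training session. Research assistants may make a separate contact, and coverage is then complete. A check on a day without a session is not a missing check. The schedule figure is not shown in the text at hand, and visit logistics and session forms commonly sit in a full protocol. All of this stands, and it limits the point. Four stronger readings are tempting and are not supported:

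- **That at most 5 of 8 checks can be met.** This needs checks only at training visits, on fixed or Monday-to-Friday weekdays. Neither condition is stated.
- **That nothing is asked after the current.** The article is silent here; it does not rule the question out. Staff are present, and the general adverse event paragraph is not limited to the 48 h screen.
- **That early events reach the record only through staff who know the arm.** Only those administering stimulation are said to be unblinded. The status of the group assistant and the screening assistants is not given.
- **That the comparison between arms is biased by design.** Both arms have the same stimulation sessions and the same screening rule.

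It is also fair to say that harms are neither a primary nor a secondary outcome. Participants must be able to give informed consent, which argues against assuming very poor recall.

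What the defence does not remove is the ambiguous wording, the missing place and mode, and the absence of any described active question close to the current. The general recording paragraph names no time and no question, so it does not replace one.

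**Conclusion.** The point holds in a limited form. The one active harm check described is fixed at 48 h and at two items, can be read in two ways, and has no stated place or mode. Carried out at training visits on a fixed timetable, it would fall on a visit for 5, 3 or 0 of the 8 stimulation sessions, depending on the gap. With varying weekdays that include Saturday it could reach 7. With separate contacts it reaches 8, at up to 496 contacts that the article does not describe. In each case, effects during or just after the current depend on general recording or on recall two days later, so harm counts may be too low. By how much cannot be said from the documents.

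A reader might infer that harm data will be incomplete or will differ in quality between arms. The text supports neither statement. This is an inexpensive improvement to data capture; it does not affect the efficacy analysis.

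**What to change.** Amend Risk monitoring as follows.

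1. Record scalp skin and headache when the electrodes are removed at each stimulation session.
2. Record the same two items on arrival at the next session, before any electrodes are placed, covering the time since the last session. Every stimulation session has a later training visit (session 11 is followed by session 12), so this works on any timetable. Note the date and time, because the interval varies.
3. Use the same short form in both arms, completed where feasible by an existing assistant who is not told the arm.
4. State whether the 48 h contact is a single one and how it is made. It can stay as an addition if wanted; it is useful where the next visit is more than 48 h away.

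The cost is protocol wording, one short form and a few minutes per session: 8 × 2 = 16 entries per participant, all at visits already planned. The change concerns only when adverse event data are captured. Clinical action on any event stays with the investigators.

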#### Adverse event and serious adverse event recording and reporting

Possible adverse events and other unintended effects of the trial will be documented in the medical records and periodically reported to the Scientific Ethics Committee. The expected hazards in this trial, according to safety guidelines, were skin damage on the skull where the electrodes were placed and mild headache. If unexpected events occur, we will use MedDRA in the trial publication to report all adverse events. Lethal or severe adverse events will be reported to the Health Services of the Region of Valparaíso (Chile) and the Scientific Ethics Committee as soon as possible or within 7 days of getting informed of the adverse event.

### Frequency and plans for auditing trial conduct {23}

The research will be audited biannually through the procedures established at the Clinical Studies Centre of the Faculty of Medicine of the Clínica Alemana—Universidad del Desarrollo (Chile).

### Plans for communicating important protocol amendments to relevant parties (e.g. trial participants, ethical committees) {25}

If any changes to the protocol become necessary, we will seek sponsor approval for the proposed amendments before submission. We will then prepare a request to the Research Ethics Committee through our local system (https://medicina.udd.cl/comite-etico-cientifico/), authorised by both the CI and the sponsor. The CI will promptly communicate the outcomes of the review process and any resulting protocol modifications to the participating sites and relevant organisations. Furthermore, we will update the trial registrations and the published protocol to reflect these amendments accordingly.

### Dissemination plans {31a}

The trial data has the potential to shape changes in the current approach to addressing MCI and to slow down the progression of Alzheimer’s dementia. The assessment of treatments for patients will further facilitate the training and dissemination of this approach, not only within MCI but also in other relevant contexts. Insights gained from qualitative analyses will provide valuable information regarding its feasibility. The research findings will be disseminated widely and published in peer-reviewed scientific journals and professional publications. We will also present our results at conferences and workshops and, when feasible, share our findings through various media and social media platforms. Additionally, we are committed to sharing these findings at the local level with participants, healthcare services and other stakeholders.

## Discussion

Globally, a notable sociodemographic transformation is in progress, primarily defined by an ageing population and changes in the epidemiological profile, leading to a heightened prevalence of chronic diseases and neurological conditions, including dementia and mild cognitive impairment (MCI). These conditions carry substantial socioeconomic implications for patients and indirectly impact their families and society.

MCI can be viewed as an early stage of certain dementias, making it a crucial point for implementing interventions aimed at delaying cognitive decline, reducing dependence, and preserving the quality of life. A critical cognitive facet open to intervention is working memory, a fundamental element of daily executive functioning and a gateway to long-term memory preservation. Consequently, there is growing interest in assessing the impact of specific interventions in this cognitive domain.

One promising approach to address this challenge involves combining techniques that have individually demonstrated efficacy in enhancing memory performance [57, 58]. As such, this project proposes a range of cognitive training methods and NIBS techniques. Both strategies have shown positive effects in older adults, supporting that the ageing brain can be selectively and enduringly trained [59–62]. Specifically, we will investigate the effects tACS in conjunction with personalised and progressive cognitive training [33, 36, 63–65].

For instance, Grover et al. [36] illustrated the repetitive use of transcranial alternating current stimulation (tACS) over 4 days, leading to a sustainable improvement in auditory-verbal working memory and long-term memory in individuals aged 65 to 88. Notably, the modulation of synchronous low-frequency activity in the parietal cortex resulted in a preferential enhancement of working memory on the third and fourth days, as well as 1 month after the intervention.

In summary, this project aims to provide insights into the combined impact of cognitive training and transcranial alternating current stimulation on MCI outpatients. Regarding this neuromodulation technique, the study seeks to delineate highly localised spatial-spectral parameters of memory-specific cortical circuitry, equipping clinicians with practical tools to intervene in MCI patients.

## Trial status

The project officially started on January 5, 2019, with Consent Version No. 3 being signed on October 30, 2019. However, recruitment was delayed until January 26, 2022, owing to the impact of the COVID-19 pandemic. We project the recruitment phase to conclude by January 26, 2024, with the overall study ending on December 30, 2024.

## Availability of data and materials {29}

The datasets produced and analyzed during the present study are not publicly accessible due to the ongoing status of the protocol at the time of submission. The Clinical Investigator will serve as the custodian of the trial data, and any data necessary to support the protocol can be provided upon request.

## Abbreviations

CAFUV: Center of Phonoaudiological Attention of the University of Valparaiso
CCTP: Combined cognitive training programme
MCI: Mild cognitive impairment
NIBS: Non-invasive brain stimulation
PI: Principal investigator
SMP: Successful memory performance
tACS: Transcranial electrical stimulation of alternating current
TCTP: Traditional cognitive training programme
tDCS: Transcranial direct current stimulation
TMT-B: Trail Making Test B
WM: Working memory
